### Recruitment

All people with asthma who are under the care of the asthma service at Portsmouth Hospitals University National Health Service (NHS) Trust will be invited to participate in this study. This will include recruitment from primary care sites. In addition, both outpatients and inpatients will be approached and invited to participate.

### Study Assessment

This section describes the information that will be recorded in the participant’s RedCap report, which will be anonymized using the participant’s unique study number.

#### Participant Clinical Characteristics

The following information is routinely collected and used as part of standard care and following consent and recruitment to the study will be transcribed from a participant’s clinical care records and will be recorded on the e-CRF.

#### Patient Details and Demographics

Age, gender, ethnicity, school or work status, educational levelSmoking status and pack-year smoking historyAsthma severity is defined using British Thoracic Society stagesNew or established patients to the asthma serviceMedical comorbidities

#### Asthma Characteristics

Age when asthma diagnosis was madeSpirometry—this will either be captured as part of their routine clinic visit or can be historic (within the last 12 months)Type 2 (T2) biomarkers: peripheral blood eosinophil count and fractional exhaled nitric oxide (FeNO)—this will either be captured as part of their routine clinic visit or can be historic (within the last 12 months)Number of exacerbations in the preceding 12 months (number of courses of steroids, number of emergency department attendances or hospital admissions)Current asthma treatments

#### Adherence Assessment

Medicines possession ratio (MPR)—this measurement will consider the past 12 months of the participant’s adherence. Adherence will be defined as an MPR ≥80%Advanced measures of adherence (such as FeNO suppression) where available

#### Complexity of Medication Regime

Total number of medications taken each dayNumber of doses of inhaled medications per day

#### Questionnaires Collected

The asthma COM-B questionnaire [13] measure will be responsible for identifying one’s capabilities, opportunities, and motivations regarding asthma medication adherence. In the questionnaire, these measures will be presented as individual questions, forming 6 matrix tables.

This questionnaire will be brief, with 6 items asking them to rate their understanding of their psychological and physical capacities, opportunities, and motivations for adhering to asthma treatment on a Likert scale (see Figure 3, for example items from the questionnaire adapted from Keyworth et al’s [17] COM-B measure). This tool would follow the structure, formatting, and length of other questionnaires given to patients during their initial assessments. As a result, it will be easily integrated into the health care system, providing health care providers with immediate responses to patients’ psychological needs and potentially getting a better understanding when meeting with the patient.

The ACQ [15,18] consists of 6 items covering day and nighttime symptoms, activity limitations, and rescue bronchodilator use. A score of ≥1.5 reflects poor asthma control.

The Mini Asthma Quality Of Life Questionnaire standardized version [16,19] measures four domains: symptoms, activity limitation, emotional function, and environmental stimuli.

**Figure 3 figure3:**
[figure not shown]
Items 1 of 6 from the adapted capability, opportunity, and motivation model of behavior change questionnaire to target known drivers of adherence in people with asthma. This figure was adapted from Keyworth C et al [17] which is published under Creative Commons Attribution 4.0 International License [20].

#### Adherence Measures

The 61-item Theoretical Domain Framework Questionnaire [21,22] will determine the individual’s behavior in terms of the theoretical domains framework (see Table 1).

The Test Of Adherence To Inhalers [23,24] is a 12-item questionnaire designed to assess adherence to inhalers in patients with asthma.

#### Digital Readiness Measure

The Digital Readiness Scale [17] was followed to investigate the effectiveness of using technology tools for medical practices in the NHS. This scale will be adapted to 6 items assessing participants’ use of digital tools, interest in digital tools, and challenges faced by participants while using digital tools [25].

### Statistical Analysis

#### Data Exclusion

Participants are free to withdraw from the study, and this will not affect their treatment. Participants will consent at the start of the survey to allow their anonymized study data to be retained and analyzed by the study team if they withdraw from the study. Withdrawn participants will not be replaced.

Data will be analyzed once 146 participants have completed the questionnaire. All data will be handled within the general data protection regulations conditions, which came into force in May 2018.

Once a survey is completed, it is locked, and time-stamped so the survey responses cannot be edited further. Required fields are specified on the survey form, and partial or incomplete responses will not limit the survey response. Once the survey response limit is reached, the public URL will redirect to a message notifying that the survey is closed.

#### Data Management

All data collection will be completed on the web. The research team will use the Redcap electronic cloud solution to store and manage all consent and study data. The cloud services are NHS compliant and approved for use in surveys.

Data will be stored on a secure password-protected electronic research database hosted on a secure NHS server with appropriate backup systems, antivirus software and security protocols compliant with NHS information governance standards. Data entered into the electronic database will be accessible only by a restricted number of research personnel listed in the delegation log of the survey master file.

There will be a survey master file with a delegation log of approved users in the file. Before anyone can use the database, they will have to be included in this list, with the approval of the chief investigator. The chief investigator and survey coordinator will have access to all research data collected in this study to perform the data analyses required.

A data manager will perform regular data quality control checks, and reporting and statistics will be performed using tools built into the survey distribution platform. A comprehensive audit log will be maintained throughout the study and exported and stored in the survey master file on study closer.

##### Overview

Patient scores for the behavioral components of physical capability, psychological capability, social and physical opportunity, and reflective and automatic motivation will be tabulated, so that adherence and asthma characteristics can be recorded for each behavioral source against predefined behavioral change techniques based on the behavioral change wheel [12].

##### Summary Statistics

Demographics or baseline characteristics of each participant will be produced, as well as summaries for all participants combined. Normally distributed continuous variables will be summarized by the mean to characterize the population. Nonnormally distributed variables will be summarized by the median to characterize the population.

##### Primary Analysis

The primary analysis will comprise the correlation of outcomes from the brief COM-B questionnaire and the TDF questionnaire, as well as the Spearman rank correlation coefficients (ρ; strength of the relationship) and a hierarchical multiple regression analysis. For example, the capability result of the questionnaire will be compared to knowledge, skills, memory attention and decision processes, behavioral regulation, and skills. In addition, some exploratory analysis between the variables will be conducted—this will be used to derive the content validity of the brief COM-B questionnaire.

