### Overview

This study will assess whether the brief COM-B questionnaire can identify the same psychological and behavioral barriers as the current longer questionnaires (barriers to medication adherence questionnaire) and therefore assess the COM-B questionnaire’s ability to identify any important factors that may need to be addressed to support patients to take their asthma treatments as recommended.

We will also see whether there are any links between the type and severity of asthma that someone has, their other medical problems, how much treatment they have to take each day, and the COM-B questionnaire responses. This may help us better identify people who may struggle to take their medications properly and why. Again, we will use information routinely collected in the clinic, including lung function test results and medication prescription reviews, to do this.

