## Methods

### Overview

This study will employ a cross-sectional survey design focusing on adherence to asthma treatment. It will be delivered through REDCap, a web-based platform. Participants will be recruited when attending their routine clinical review with the asthma service or while an inpatient at Queen Alexandra Hospital in Portsmouth, United Kingdom. Routinely collected patient data, including demographics, asthma characteristics, asthma control, and medication regime that is already collected as part of their clinical review, will be recorded on an electronic data capture form (e-CRF) through the REDCap platform. They will then be asked to complete the series of questionnaires, all completed on the web. Patients will also be provided with a paper copy of each questionnaire. When the questionnaire is completed, the user will be provided with debriefing information.

Participants will be asked to complete a set of questionnaires that will assess the following:

Psychological and behavioral barriers that may affect the participant being able to take their asthma treatments as recommended: the brief COM-B questionnaire (which is being validated as part of this study) and the 61-item Theoretical Domain Framework Questionnaire.Their asthma symptoms and how well controlled their asthma is (Asthma Control Questionnaire [ACQ-6]), the impact their asthma has on their quality of life (Mini Asthma Quality of Life Questionnaire), and the level of anxiety or depression they may be experiencing (Hospital Anxiety and Depression Scale). All of these questionnaires are used routinely at clinic reviews.Their use of technology at home and any challenges they face with this: Digital Readiness Questionnaire.

The COVID-19 pandemic has changed the way people with asthma access their care with a move to remote consultations and questionnaire completion. The COM-B questionnaire may well be suitable for this approach. However, it is essential to assess digital readiness in this population to understand whether this is feasible and inform the design of future studies if the COM-B questionnaire proves to be successful.

It should not take more than 20 minutes to complete. The questionnaires are all validated and approval has been granted for their use in this study.

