### Sampling and Sample Size

A power calculation was conducted to determine the sample size, using the 6 components of the COM-B model that are hypothesized to drive behavior, namely physical capability, psychological capability, physical opportunity, social opportunity, reflective motivation, and automatic motivation. Using the G-power analysis for 6 predictors, a minimum of 146 participants are needed. The G-power analysis was run using SPSS to offer a sensitivity power analysis of the effect size that this sample size was sensitive to detect.

As a result, to detect a standardized effect size of Cohen ​*d*=0.43 with 80% power (α =.05, 2-tailed), G*Power suggests we would need 146 participants in independent tests. A paired sample *t* test with 30 participants would be sensitive to the effects of Cohen *d*=0.53 with 80% power (α=.05, 2-tailed). This means the study would not reliably detect effects smaller than Cohen *d*=0.53. To detect a Pearson correlation coefficient of ρ=.21 with 80% power (α=.05, 2-tailed), G*Power suggests we would need 146 participants.

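### The primary analysis measures association between COM-B and TDF scores across patients, which cannot by itself show that the two questionnaires identify the same barriers in a patient

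*Protocol article*

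**What the plan says.** The Introduction's Overview sets the question: "This study will assess whether the brief COM-B questionnaire can identify the same psychological and behavioral barriers as the current longer questionnaires". The Methods Overview names the two instruments compared: "the brief COM-B questionnaire (which is being validated as part of this study) and the 61-item Theoretical Domain Framework Questionnaire". The intended use is individual. The Objective speaks of detecting a patient's own perceived barriers, Questionnaires Collected expects providers to receive immediate answers about a patient's needs, and the Conclusions look to individualized interventions.

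Under Primary Analysis the plan opens with score correlations: "The primary analysis will comprise the correlation of outcomes from the brief COM-B questionnaire and the TDF questionnaire". Rank correlations and a regression model are named as further parts of that primary analysis. The example compares the capability result with the TDF domains mapped to it. Unspecified exploratory work is added, and "this will be used to derive the content validity of the brief COM-B questionnaire".

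Sampling and Sample Size gives the only correlation size in the document: "To detect a Pearson correlation coefficient of ρ=.21 with 80% power (α=.05, 2-tailed), G*Power suggests we would need 146 participants". The article states no minimum correlation that would count as good convergence, no score that marks a barrier on either instrument, and no measure of agreement.

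**The concern.** Finding the same barriers is a statement about what two tools say of one patient. A correlation says that patients who score higher on one tool tend to score higher on the other. Two questionnaires on the same behaviour, answered by the same people at one visit, can be expected to correlate to some degree, so a coefficient above zero tells us little. Even a moderate one leaves open how often the short tool misses a barrier that the long tool finds.

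The secondary and exploratory analyses do not fill the gap. They compare levels of the COM-B components, relate COM-B to adherence, and examine networks with asthma characteristics. None sets COM-B against the TDF patient by patient. At stake is whether the study can answer its own question: a six-item tool meant to guide individual care could be described as finding the same barriers on evidence that does not bear on that claim.

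**Working it through.** **Inputs from the article.** N=146; ρ=.21; 80% power; two-tailed α=.05; six COM-B items, one per component.

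**Assumptions, because the article gives no figures.** Bivariate normal scores for each component; a barrier flag at the lowest quartile on each tool; true matched correlations of .21, .50 and .70 as a range.

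**1. The plan's own figure.** By Fisher's z, N = ((1.960+0.842)/atanh(.21))² + 3, with atanh(.21)=0.2132. This gives 175.7, so 176 and not 146. Power at 146 is about 72%. That discrepancy is a separate matter. What counts here is that sizing to detect ρ=.21 implies a null of zero, and that .21² = 4.4% shared variance.

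**2. What significance against zero would require at N=146.** Critical |r| = t/√(144+t²) with t=1.977, which is 0.163. Shared variance is 0.163² ≈ 2.6%.

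**3. Patient-level overlap for one component.** Let p be the probability that both scores fall in their lowest quartile. The share of TDF-flagged patients whom COM-B also flags is p/.25. With equal margins, chance agreement is .25²+.75² = .625, so kappa = (2p+.50−.625)/.375.

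| True ρ | p | Flagged by COM-B among TDF-flagged | Kappa |
|---|---|---|---|
| 0 (chance) | .0625 | 25% | 0 |
| .21 | .0848 | 34% | 0.12 |
| .50 | .1203 | 48% | 0.31 |
| .70 | .1504 | 60% | 0.47 |

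At ρ=.50 the short tool still misses about half of the patients the long tool flags.

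**4. Agreement on the single lowest component.** Simulation of six components with matched ρ=.50 and within-tool correlation 0.4 (both assumed), varying the correlation u between unmatched components across tools:

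| u | Same lowest component (chance 16.7%) |
|---|---|
| .10 | 48% |
| .20 | 37% |
| .30 | 29% |
| .40 | 23% |

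The same matched correlation is therefore compatible with about 23% to 48% agreement. The matched coefficient does not determine concordance, and no single figure should be quoted for it.

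**5. Precision available at N=146.** The 95% interval is tanh(atanh(r) ± 1.96/√143). For observed r of .21, .50 and .70 this gives 0.05 to 0.36, 0.37 to 0.61, and 0.61 to 0.77. Intervals for Spearman's coefficient are slightly wider. The sample can therefore support a judgement on the size of the correlation.

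**The case against.** Correlating a short scale with a longer one, matched by domain, is standard evidence of convergent validity, and the coefficients should stay. Thresholds, cut-offs and agreement tables are often left to an analysis plan, which may exist. Both points stand. What remains is that the article itself fixes the aim and the type of primary analysis, and the two do not match.

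Several stronger readings are tempting but not supported:

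- *That the tool will be declared valid once a correlation differs from zero.* Primary Analysis states no null and no success rule, and calls Spearman's ρ a measure of strength. The zero null is inferred from the sample-size section. A ρ of .21 could equally be reported as weak convergence.
- *That the plan does nothing but correlate.* It also names a hierarchical regression and exploratory work. The regression is again a measure of association and the exploratory work is not described, so neither closes the gap, but they are there.
- *That the tools would disagree on most patients' main barrier.* The article does not define a single main barrier per patient, and several may coexist. Agreement on the lowest component depends on correlations that the article does not give, and single Likert items will produce ties.
- *That every component must clear one fixed bound.* Any such bound is a choice for the study team to justify.

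**Conclusion.** The point holds in this limited form. The aim asks whether two tools identify the same barriers; the primary analysis estimates association across patients; and the only correlation size stated, ρ=.21, is 4.4% shared variance. Under normality and a lowest-quartile flag, correlations of .21, .50 and .70 correspond to COM-B finding 34%, 48% and 60% of TDF-flagged patients, against 25% by chance. The exact percentages would change with another cut-off or with coarse Likert scores. The conclusion that correlation does not establish agreement would not. This is a low-risk, single-visit questionnaire study and the remedy uses data already being collected, so the point should be fixed but does not undermine the study.

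**What to change.** 1. Keep the matched Spearman coefficient for each of the six components and report each with a 95% confidence interval. Judge convergent validity by size, against a minimum justified before analysis, and not by significance against zero.
2. Add to Primary Analysis a patient-level concordance analysis for each component: percent agreement, kappa, and the sensitivity and specificity of COM-B low-score flags against the mapped TDF score.
3. Before analysis, fix the cut-off on each tool, the handling of ties among single Likert items, and the handling of TDF domains that Table 1 places under two components (skills in both capability components; role and identity, and optimism, in both motivation components).
4. If this is not done, limit the conclusion to association and do not claim that the tools identify the same barriers.

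**Cost.** Wording and a little programming, with no new data. Precision will be modest: a quartile flag leaves about 146 × .25 ≈ 36 flagged patients per component, so a sensitivity of 48% carries about ±1.96 × √(.48 × .52/36) ≈ ±16 percentage points. The validity statement may also turn out less favourable.

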### Ethical Considerations

#### Statement of Compliance

All staff working on this study will hold evidence of good clinical practice training before undertaking any responsibilities, and all staff working within the research study team are also part of the respiratory clinical care team and are involved in PhD supervision. Written informed consent will be obtained from all participants after an adequate explanation of the aims, methods, and anticipated benefit of the study using the participant information sheet. A signed copy of the consent form will be given to the participant, and copies will be filed in the study master file and the participants’ medical notes.

Participants’ anonymity will be maintained throughout by identification on a password-protected electronic database and e-CRFs only by initials and participant ID number. All documents will be stored securely and only accessible by study staff and authorized personnel; the study will comply with the Data Protection Act.

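### As described, the primary analysis cannot by itself show that the COM-B questionnaire tells one adherence barrier from another, because no off-domain contrast is stated

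*Protocol article*

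**What the plan says.** **Aim.** The Overview at the end of the Introduction states: "This study will assess whether the brief COM-B questionnaire can identify the same psychological and behavioral barriers as the current longer questionnaires". Under Statistical Analysis, the Overview of the analyses adds that the component scores will be tabulated against predefined behaviour change techniques, so the result is meant to guide what is done for each component.

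**Primary analysis.** The general statement is: "The primary analysis will comprise the correlation of outcomes from the brief COM-B questionnaire and the TDF questionnaire". It adds Spearman coefficients and "a hierarchical multiple regression analysis", with no outcome, blocks or predictors given. One comparison is spelled out, introduced as an example: "the capability result of the questionnaire will be compared to knowledge, skills, memory attention and decision processes, behavioral regulation, and skills". Finally "some exploratory analysis between the variables will be conducted", offered as evidence of content validity.

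**Instruments.** COM-B has six items, one per component (Questionnaires Collected). The TDF questionnaire has 61 items. Table 1 maps the 14 TDF domains to the six components.

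**Elsewhere.** The Secondary Analysis compares mean levels of the components and relates COM-B to adherence. The Exploratory Analysis lists a network analysis of mainly clinical variables. Neither is presented as a test of whether a component follows its own domains more closely than the others.

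**The concern.** A correlation between a component and its own domains is convergent evidence. Identifying a patient's barrier also needs discriminant evidence: the capability item should follow the capability domains more closely than it follows, say, the emotion or social influence domains.

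Here there is a plausible rival explanation for any mapped correlation. Both instruments are self-report and are answered in the same visit. The Statement of Compliance says that "all staff working within the research study team are also part of the respiratory clinical care team", which may encourage favourable answers. A patient inclined to answer everything positively, through mood, general attitude or a wish to please, raises every COM-B to TDF correlation, mapped or not. With one item per component, nothing inside COM-B can separate the specific part from the general part.

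At stake is the intended use. If the scores carry mainly a general attitude, the flagged component may be unrelated to the patient's actual barrier, and the intervention chosen for it would rest on noise.

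**Working it through.** **1. The plan's own figure.** Sampling and Sample Size gives N=146 for a Pearson correlation of 0.21 at 80% power, two-sided 0.05. By Fisher's z, n = ((1.960 + 0.842)/atanh(0.21))² + 3 = (2.802/0.2132)² + 3, which rounds up to 176. With N=146 the power is Φ(0.2132·√143 − 1.960) = 72%. The figure does not reproduce, but that is a separate matter. The present point takes N=146 only as the number of participants to be analysed.

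**2. The mapping.** Mapped domains per component in Table 1: psychological capability 4, physical capability 1, social opportunity 1, physical opportunity 1, reflective motivation 6, automatic motivation 4. The total is 17 mapped cells out of 6 × 14 = 84, leaving 67 unmapped. Skills, social or professional role, and optimism each appear under two components (14 + 3 = 17). Skills is the only domain mapped to physical capability.

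**3. A general response tendency alone.** Simulation: 2,000 runs per setting, N=146, six COM-B items and 14 TDF domains. All COM-B to TDF correlation comes from one common factor, equally strong for every item and domain, with no component-specific signal. The factor's strength and the rounded 0–10 item scale are assumptions; the article says only that the scale is Likert. Tests are Spearman, two-sided 0.05.

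| Assumed general correlation | Mean ρ mapped / unmapped | Mapped correlations significant | All 17 significant |
|---|---|---|---|
| 0.1 | 0.09 / 0.09 | 21% | 0% |
| 0.2 | 0.19 / 0.19 | 62% | 0.4% |
| 0.3 | 0.28 / 0.28 | 94% | 43% |
| 0.4 | 0.38 / 0.38 | 99.8% | 96% |

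Hand check of the third column. The critical ρ is 1.977/√(144 + 1.977²) = 0.163, or 0.164 on the z scale, with standard error about 1/√143 = 0.0836. At mean ρ = 0.283, z = (0.291 − 0.164)/0.0836 = 1.52, giving 94%. At 0.094, z = (0.094 − 0.164)/0.0836 = −0.83, giving 20%.

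**4. Does regression rescue it?** Regressing the psychological capability item on its four mapped domains, under the same general factor, is significant in 35%, 89%, 99.7% and 100% of runs. A regression confined to mapped domains has the same blind spot.

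**5. What does separate the cases.** Take a general correlation of 0.3 and add a component-specific signal (assumed share 0.4). Mean ρ becomes 0.52 mapped against 0.28 unmapped, a difference of 0.24. With no specific signal the difference is 0. In separate general-factor-only simulations, the standard error of this difference per component was about 0.03 to 0.06 with loadings of 0.6 (COM-B) and 0.7 (TDF), and 0.035 to 0.07 with 0.5 and 0.6. The study as sized can therefore estimate the contrast usefully.

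**The case against.** A reader might infer that the plan restricts itself to mapped comparisons. The documents do not support that. The capability comparison is introduced as an example, the governing sentence does not exclude the full matrix, and the regression and exploratory work are open enough to include other domains. A reader might also infer that a general tendency would be accepted as validity. That does not follow either: the article states no threshold, significance rule or other pass criterion.

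Further, this is a condensed article and an analysis plan may exist; which cells are reported and which contrast is tested are often settled there. The simulation sets specific signal to zero, so equality of mapped and unmapped means is built in and says nothing about these patients. No factor strength comes from the documents, and at 0.1 to 0.2 many mapped correlations would not be significant. Answers are self-completed electronically, and the staffing statement does not say that the treating clinician administers the forms. The Secondary Analysis also relates COM-B to the medicines possession ratio and FeNO suppression, which are not self-report.

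All of this stands and limits the claim. It does not remove the gap. The adherence measures test whether COM-B relates to adherence, not which barrier it detects. The comparison that answers the primary question belongs in the protocol, and an analysis plan could follow this description faithfully and leave the aim untested.

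**Conclusion.** The concern holds in limited form. The article describes COM-B to TDF correlations, illustrates them with one component against its own domains, and states no off-domain contrast. That yields convergent evidence, which cannot by itself show that COM-B distinguishes barriers.

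The size depends on an unknown, the strength of any general response tendency. From about 0.3 upwards it alone makes about 94% or more of the mapped correlations significant at N=146; at 0.1 it makes about 21% significant. The share with all 17 significant is more sensitive, falling from 96% at 0.4 to 43% at 0.3. These figures assume one common factor, equal loadings and a 0–10 item scale. They show that mapped correlations are ambiguous, not that COM-B fails to discriminate. This is a worthwhile, inexpensive improvement to the primary analysis.

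**What to change.** In the Primary Analysis section:

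- Report the full 6 x 14 Spearman matrix, with the 17 mapped cells marked in advance from Table 1.
- For each component, estimate mean mapped minus mean unmapped correlation with a bootstrap 95% interval, resampling patients.
- Describe a component as distinguished only if the lower limit exceeds zero, with a stated multiplicity adjustment over the six components. Bonferroni, for instance, would base that decision on 1 − 0.05/6 = 99.2% intervals.
- As support, report the mapped correlation adjusted for the patient's mean score on the unmapped domains only. A mean over all 14 would contain the mapped ones (6 of 14 for reflective motivation) and remove real signal.
- Note that skills, social or professional role, and optimism each map to two components. Skills alone cannot separate physical from psychological capability.

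The contrast is zero under a general factor only if that factor affects all domains about equally, so it should be read beside the full matrix, where a domain that correlates highly with every component will show.

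The cost is a little more analysis, with no new data or participants. Some components may have to be reported as not distinguishable.
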